#### Montreal Cognitive Assessment

This measure will be completed at baseline only to allow us to describe the cognitive profile of participating PWD [22].

#### Modified Falls Efficacy Scale

The psychological consequences of falling will be determined using the Modified Falls Efficacy Scale (MFES) [23]. This is a 14-item measure of falls efficacy (or fear of falling), based on the original Falls Efficacy Scale [24].

#### Goal Attainment Scaling

As part of the intervention, therapists will set individualised goals with participants. The goals will be agreed with the PWD by the therapists at the first therapy session and assigned ‘weights’. Goal Attainment Scaling (GAS) is a method of scoring the extent to which these goals are achieved in a way that is standardised for analysis [25, 26]. Progress towards goals will be measured at the final intervention visit, allowing a numerical score to be calculated at 12 weeks.

#### Generic Quality Of Life Instrument

The EuroQol-5 Dimension-5 Levels (EQ-5D-5L) is a standardised instrument used to measure generic health-related quality of life [27]. The five dimensions are mobility, self-care, usual activities, pain/discomfort and anxiety/depression. The five levels range from no problems to extreme problems.

#### Quality of Life–Alzheimer’s Disease Scale

The Quality of Life–Alzheimer’s Disease Scale (QOL-AD) is a standardised instrument for measuring quality of life for PWD [28, 29]. It is a 13-item scale administered via an interview. It includes the domains of physical condition, mood, memory, functional abilities, interpersonal relationships, ability to participate in meaningful activities, financial situation and global assessments of self as a whole and QOL as a whole.

### PWD outcome measures completed by an informal carer

With the exception of the Health Utilisation Questionnaire, all outcome measures will be completed by an informal carer at both baseline and 12-week follow up.

#### Disability Assessment For Dementia

The Disability Assessment for Dementia (DAD) is a standardised instrument measuring the functional ability of PWD in activities of daily living (ADLs) [30]. It is 40-item scale administered via an interview with a proxy.

#### EQ-5D-5L proxy

The proxy version of the EQ-5D-5L will be completed by informal carers regardless of whether or not the PWD lacks capacity.

#### QoL-AD proxy

The proxy version of the QoL-AD will be completed by informal carers regardless of whether or not the PWD lacks capacity.

#### Health Utilisation Questionnaire

This questionnaire will be completed by the clinical researchers using information from informal carers at 12 weeks to ascertain which additional health and social care services have been used by the PWD during the 12-week period of the intervention. We will use informal carers as proxy respondents since it is unlikely that many PWD will be able to provide detailed information about retrospective service use. To facilitate recall, we have included a section for health and social care appointments in the prospective diary. This will be a pilot of the questionnaire for a future definitive trial.

### Informal carer outcome measure

#### Zarit Burden Interview

Carer burden will be measured using Zarit Burden Interview (ZBI), a series of 22 questions designed to elicit the impact of the patient’s disabilities on the life of the caregiver [31]. This will be completed with informal carers at baseline and follow-up.

### DIFRID intervention

#### Description of the DIFRID intervention

An overview of the intervention is provided in Fig. 1. Details of the intervention are supplied in Additional file 3. The intervention will be a multidisciplinary intervention primarily delivered in the participant’s home. The intervention will be tailored to the abilities of the participant, their likes and dislikes for activities and goals agreed between the therapist and the participant and their informal carer. The number of sessions will be tailored to the needs of the participant; the first two sessions will be assessment sessions followed by up to 22 therapy sessions delivered over a total period of up to 12 weeks. The assessment and therapy procedures are described in a bespoke manual for professionals (Additional file 4).

**Fig. 1 Fig1:**
[figure not shown]
Overview of the DIFRID intervention

### Feasibility outcome measures

#### Feasibility of recruitment and retention

We will explore the feasibility of different approaches to PWD identification and recruitment. We will also consider the rates of conversion to study participation and retention. Specifically, we will report on:The number of PWD identified through community and secondary care, and case registers/JDRThe proportion of PWD who give permission for us to check their medical records to determine eligibilityThe proportion of PWD who meet the eligibility criteriaThe proportion of eligible PWD who agree to participate in the studyThe proportion of eligible informal carers who agree to participate in the studyThe proportion of participating PWD and informal carers who start the interventionThe proportion of participating PWD and informal carers who remain in the study until study completionThe proportion of participating PWD and informal carers completing each outcome measure at baseline and 12-week follow-up

CTAs responsible for recruitment and professionals responsible for the initial approach to potential participants will be invited to take part in a formal interview to explore the feasibility and acceptability of the different approaches to patient identification.

#### Assessment of suitability and acceptability of outcome measures

We will also examine the response rates, acceptability and feasibility of outcome measures described in Table 1 that could be used in a definitive trial. We will include a small number of open questions at the final follow-up interview to explore their views on the measures used and to identify any additional outcomes of the intervention that have not been captured. The clinical researchers responsible for collecting outcome data will also be invited to take part in a brief qualitative interview to give their feedback on the outcome measures.

#### Assessment of the feasibility and acceptability of intervention delivery

Since the intervention is multi-dimensional and tailored to the individual, we will use mixed methods and seek the views of a range of stakeholders. Quantitative analysis will consider:The proportion of staff attending all training and supervision sessions and MDT meetingsThe number, frequency and duration of training and supervision sessions, and MDT meetingsTime spent with the patient and time spent travelling to appointmentsThe proportion of patients discussed at MDT meetings and actions takenThe proportion of patients seen by a geriatricianThe proportion of patients reviewed by the MDT at six and twelve weeks and actions takenHow the assessment documentation was used in practice, for example, whether all sections were completedThe nature of goals set and alignment of activities with these goalsReferrals made to other servicesAdherence with agreed activities by PWD

Additional qualitative work will provide a more nuanced understanding of these data and allow us to explore whether and how the intervention will need to be adapted prior to a full trial. We will either directly observe or use audio recordings of intervention training, delivery and supervision in all sites; this will enable us to explore adherence and variation between and within sites. Observation will be supplemented with semi-structured interviews with a range of stakeholders to explore:The ‘fit’ of the intervention with staff usual working practicesThe acceptability of the intervention and suggested changes or improvements to the content, delivery or timing of the interventionAssessment of training and intervention deliveryThe feasibility and perceived value of MDT meetingsThe feasibility of different components of the intervention (e.g. goal setting and tailoring)

To ensure that we capture the views of different stakeholders, we will interview staff delivering training and supervision, staff delivering the intervention, members of the MDT, PWD and informal carers receiving the intervention and health and social care staff who are concurrently providing care to the PWD and/or to whom the PWD is referred during the intervention.

In a previous process evaluation [32], we found informal discussions to be a very effective way of collecting data in a timely fashion. Such discussions may only last a few minutes but can deepen understanding of how the intervention is being delivered. We anticipate that informal discussions will be conducted throughout the WP4 with staff responsible for training and supervision and those responsible for intervention delivery.

### Process evaluation

Interviews will explore the acceptability and perceived value of the intervention to PWD and their informal carers. Topic guides are given in Additional file 5. We will also explore the extent to which participants felt the intervention was tailored, their views on the intensity of the intervention and staff involved in delivering the intervention and any suggested changes to the intervention. PWD consenting to a qualitative interview will be interviewed separately from their informal carer where possible, but jointly if preferred by the participant. Interviews will take no longer than 60 min and will be audio recorded with participants’ permission (as documented on the initial study consent form; consent to recording will be verbally confirmed at the time of the interview). The clinical researcher undertaking baseline and follow-up assessments will include some open-ended questions to explore participants’ views on the outcome measures. These qualitative data will be recorded in detail on the case report form (CRF) and passed to the qualitative team for analysis.

As described above, professionals will be observed during intervention delivery (with the consent of the PWD and informal carer) and during MDT meetings. The qualitative team will also observe the initial training and some supervision sessions. The importance of observing supervision was highlighted in a previous study where it revealed specific areas in which additional training was required [32]. Information from the observation will inform subsequent interviews and informal discussions with professionals and will allow us to follow up emerging issues in more detail. Interviews with MDT members will explore the perceived value and sustainability of the MDT meetings as part of the intervention. Alternative models of obtaining specialist input will also be explored.

Interviews with professionals to whom PWD and/or informal carers have been referred as a result of the intervention and/or who have been providing care to participants during intervention delivery will explore their experiences of the intervention, the ‘fit’ of the intervention with the care they provide and suggested changes or improvements to the content, delivery or timing of the intervention. The appropriateness of referrals will also be explored.

### Withdrawal criteria

PWD and informal carers will have the right to withdraw from intervention delivery, outcome assessment and/or the (optional) qualitative component, without having to give a reason, although they may give one if they wish to do so. Investigator sites will clarify with participants which aspects of the study they wish to withdraw from and document this on a study withdrawal form.

The investigator may discontinue a participant from the study at any time if necessary.

Due to the nature of the disease, some participants may become very ill or die before completion of the study. Participants who withdraw from the trial will not be replaced routinely, but if an unexpectedly large number of participants withdraw early, it may be necessary to replace them to achieve adequate data to answer our research questions.

Professionals who are not directly involved in intervention supervision or delivery will also have the right to withdraw from the study at any time without having to give a reason.

### Adverse events

This is a non-drug intervention trial, using interventions that might be offered as part of a routine physiotherapy intervention. Dementia is progressive and associated with comorbidity. Inter-current illness will be very common. We will aim to achieve a balance between ensuring that any adverse events (AEs) which are likely to be related to the study are detected, and the recording of numerous unrelated events.

Falls, injuries, deaths and hospital admissions will be ascertained prospectively throughout the study. They will be recorded through diaries which will be reviewed regularly by the therapists and/or rehabilitation support workers.

We will define an AE as an incident, injury or symptom related to therapy sessions, or activities undertaken independently. The most likely AEs are fatigue, minor musculoskeletal symptoms or injuries such as muscle stiffness, or sprains, or increased falls though increased activity. Some conditions such as arthritis or angina may be exacerbated by exercise. AEs will be monitored by therapists and rehabilitation support workers, and reported where they occur. All serious AEs should be reported to the NHS Research Ethics Committee (REC).

### Analysis

#### Analysis population

All analyses will be conducted on an intention to treat basis, with sensitivity analyses used to investigate the impact of removing individuals who did not receive the intervention as allocated.

#### Quantitative analyses

The main analysis will be of feasibility outcomes. We will report the numbers of eligible participants seen over the recruitment period, and the resulting rates of recruitment, retention and data completion. Non completers will be characterised. We will also assess performance of potential outcome measures for a definitive trial. We will ascertain data completeness of the instruments and any potential bias in the completion of follow-up data to inform the choice of instruments in a future trial. The majority of the outcome data will be presented in simple descriptive tables presenting percentages, means and standard deviations.

#### Health economic data

During the intervention development work, a Healthcare Utilisation Questionnaire (HUQ) was developed and piloted—the format and administration of this questionnaire was adapted in light of the responses and feedback. The questionnaire will now be completed once by the clinical researcher at the 12-week follow-up visit with information provided by the informal carer. The clinical researcher will make notes on the CRF regarding the perceived value and burden of including space in the participant diary to make a note of services received as an aide memoire for completing the HUQ at the end of the study. These notes will be passed to the qualitative team for analysis. The data collected will be analysed and presented as completion rates and descriptive statistics; this will allow our results to be used for meta-analysis and systematic reviews.

The data will be analysed as completion rates and descriptive statistics. We will look at the overall response rates and the completion of each question in the data collection tools (HUQ and EQ-5D-5L). This will help us identify any potential issues with the data collection tools and suggest amendments for a future definitive trial. Descriptive statistics will be provided for each type of healthcare resource reported and will be presented as the mean number of visits and standard deviation.

We will also determine the feasibility of identifying and estimating costs associated with the intervention and resource use. Intervention costs will be based on the data provided by the therapists on number of sessions, travelling time, referrals and involvement of the MDT. This will determine the ease of cost collection for a full definitive trial.

#### Qualitative analyses

Field notes of observation and interview transcripts will form the formal data for analysis. Normalisation process theory (NPT) [33] will inform both data collection and analysis. This theory is increasingly being used in studies of the implementation of interventions in health care (www.normalizationprocess.org) including published studies from current applicants [32, 34, 35]. Normalisation process theory is valuable in highlighting whether problems with implementation reflect a lack of perceived relevance of the intervention (coherence); the unwillingness of participants to invest in the intervention (cognitive participation); difficulties in delivering the intervention, such as a lack of resource or shortfalls in skills and knowledge (collective action); or a lack of feedback on the impacts of the intervention or inability to adapt the intervention to meet local needs (reflexive monitoring). Identifying key barriers to implementation using NPT helps in deciding how best to optimise an intervention and associated training and documentation prior to further implementation.

All field notes and interview transcripts will be anonymised prior to analysis. Following the principles of the constant comparative method, data analysis will proceed alongside data collection. This will ensure that emerging themes and issues can be explored in subsequent data collection. The qualitative team will use data analysis workshops to consider data from different sources (observation; interviews with different stakeholders; informal discussions) and develop a coding frame. Some data analysis workshops will also include members of the extended team to offer different perspectives on the data. Once a coding frame has been agreed, we will use NVivo software to manage data analysis. The analyses will focus on issues of feasibility and acceptability of the intervention and will explore the extent to which views on the intervention are consistent within and between stakeholder groups.

#### Sample size consideration

The sample size for the intervention study was decided by the expert consensus panel. Their decision reflected their expertise as to how many participants would be needed to measure feasibility outcomes, balanced with the time for recruitment available during the available funding envelope and the likely potential recruitment rates estimated from our observational work in an earlier stage of this research programme. It is anticipated that ten participants per site will give us sufficient data to answer feasibility questions including estimation of potential recruitment rates, intervention adherence and rates of completion of data outcome tools.

### Criteria for progression to full trial

Stop/Go criteria have been developed for progression to a definitive trial.

Definite Go (‘green light’) defined as follows:≥ 60% of eligible participants consenting to feasibility trial≥ 80% participants attend ≥ 60% of sessions as plannedRetention of ≥ 70% of consented participants for provision of key outcome data at 3 monthsThe intervention can be delivered with fidelity, i.e. the content, frequency, duration and quality of the intervention can be delivered as set out in the intervention delivery manualAn indication from qualitative interview and focus group work that the intervention(s) is (are) perceived as acceptable to both participants and professionals

Definite Stop (‘red light’) defined as follows:< 40% of eligible participants consenting to feasibility trial< 20% participants attend ≥ 60% of sessions as planned in a given intervention armRetention of < 50% of consented participants for provision of key outcome data at 3 monthsIt is clear from the process data from participants and professionals that the intervention procedures have low fidelity in terms of content, frequency, duration and quality and that they are unfeasible to deliverAn indication from qualitative interview and focus group work that the intervention(s) is (are) not acceptable to participants and professionals

Intermediate outcomes will be defined as amber and refinement of the intervention will be undertaken in conjunction with our patient and public involvement (PPI) panel. A decision as to whether to progress to a full trial will be discussed by the Trial Oversight Committee.

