### Secondary objectives

The secondary aims of this study are to determine the recruitment and retention rates from a range of settings, to identify issues related to the suitability and acceptability of outcome measures, and to assess the factors influencing the acceptability and implementation of the intervention.

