## Methods

This is a single arm feasibility study of the study intervention. We have followed the Standard Protocol Items: Recommendation for Interventional Trials (SPIRIT) guidance [18] and the SPIRIT checklist is provided in Additional file 1. In developing the intervention and designing the feasibility study, we have followed the Medical Research Council (MRC) guidance on developing and evaluating complex interventions [19]. We provide a description of the intervention using the Template for Intervention Description and Replication (TiDieR) guidelines [20] in Additional file 2. In accordance with the MRC guidance on process evaluation of complex interventions [21], we have developed a logic model (to be reported elsewhere). The study will be carried out in three research sites, reflecting a range of National Health Service (NHS) practice to allow for generalisability.

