### Recruitment, screening and consent

We plan to recruit a minimum of 30 people with dementia (PWD) and 30 informal carers for the intervention and up to 28 professionals for the process evaluation (beginning 5th February, ending 29th April 2018). Participants will be recruited from three geographical areas in the UK (Newcastle upon Tyne, Norwich and Stockton upon Tees).

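### The progression criteria judge recruitment only by the share of eligible people who consent, so a study far short of its 30 dyads can still be a Definite Go

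*Protocol article*

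**What the plan says.** The primary objective is the decision whether to progress to a full randomised trial. Criteria for progression to full trial answers it with five green and five red conditions.

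- On recruitment, green requires "≥ 60% of eligible participants consenting to feasibility trial" and red is "< 40% of eligible participants consenting to feasibility trial".
- The other two numeric conditions are the share of participants attending enough sessions and the share of consented participants retained at 3 months.
- The last two, fidelity and acceptability, are judged from process and qualitative data.
- Results in between are amber. The section closes by saying that the Trial Oversight Committee will discuss progression.

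Elsewhere the article treats the amount and pace of recruitment as central. Secondary objectives lists the aim to "determine the recruitment and retention rates from a range of settings". Recruitment, screening and consent states: "We plan to recruit a minimum of 30 people with dementia (PWD) and 30 informal carers for the intervention". Sample size consideration adds: "It is anticipated that ten participants per site will give us sufficient data to answer feasibility questions including estimation of potential recruitment rates". The sections on feasibility of recruitment and retention and on quantitative analyses promise the numbers identified by route, the proportions passing each step, and the resulting recruitment rates.

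**The concern.** A consent share does not depend on the size of its denominator: 6 of 10 and 60 of 100 score the same. The denominator also comes late in the pathway. Under Confirmation of PWD eligibility, people identified in community settings must first return an opt-in form. Everyone must then be reached by telephone, and those not found through primary care must agree to a check of the dementia register and be on it. People lost at these steps do not enter the consent share.

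A shortage of identifiable, eligible people per site is one of the commonest reasons why a full trial cannot be delivered. If it occurred here, the study's own data would show it, but the rule that answers the primary objective would not respond to it.

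**Working it through.** **Inputs.** Minimum of 30 dyads and dates "beginning 5th February, ending 29th April 2018" (Recruitment, screening and consent). Three sites (Methods). Ten per site (Sample size consideration). Green cut-offs of 60% consent, 80% of participants attending enough sessions and 70% retention; red consent cut-off of 40% (Criteria for progression). The documents give no expected number of eligible people, so the eligible counts below are assumptions.

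**The plan's own figure.** 3 sites × 10 = 30, which reproduces the stated minimum. The size was set by expert consensus, so there is no power calculation to check.

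**Planned pace.** If the dates are the recruitment window for dyads, 5 February to 29 April 2018 inclusive is 84 days, or 12 weeks. Then 30/12 = 2.5 dyads per week, and 2.5/3 = 0.83 per site per week.

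**Smallest recruitment that meets the green consent condition.** The number needed is 0.60 × eligible, rounded up, and is compared with 30. Confidence intervals are exact (Clopper-Pearson).

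| Eligible (assumed) | Consenting | Share of 30 | 95% CI for consent |
|---|---|---|---|
| 5 | 3 | 10% | 15–95% |
| 10 | 6 | 20% | 26–88% |
| 20 | 12 | 40% | 36–81% |
| 25 | 15 | 50% | 39–79% |
| 50 | 30 | 100% | 45–74% |

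At exactly 60% consent, 30/0.60 = 50 eligible people are needed to reach the plan. Every row above passes.

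**Do the other numeric conditions catch the shortfall?** Take 6 recruited. Attendance needs 0.80 × 6 = 4.8, so 5 people. Retention needs 0.70 × 6 = 4.2, so 5 people. Both can be met, because both are shares of those recruited. On the 12-week reading the pace is 6/12 = 0.5 per week against 2.5 planned.

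**Small denominators also make green less reliable.** If true consent is 50%, which lies in the amber range, the chance of observing at least 60% is 0.38 with 10 eligible and 0.10 with 50.

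**The converse.** 30 recruited from 76 eligible is 30/76 = 39.5%. That meets the plan in full but falls under the red consent condition.

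**The case against.** Four points can be made for the plan.

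- **The committee decides.** A reader might infer that a green result launches the full trial. The documents do not support that: the Trial Oversight Committee, with 75% independent membership, discusses progression, and the Conclusions speak only of seeking funding. This stands as a real mitigation. It is incomplete because the sentence follows directly on the amber provision, so its reach to green results is unclear, and the committee is given no recruitment figure to apply.
- **The data are collected.** A reader might infer that losses before eligibility go unseen. They do not: a list of potential participants is kept at each site, and the numbers identified by route, record-check permission, eligibility and agreement are all to be reported. What is missing is their use in the rule.
- **The scenario is assumed.** Nothing in the documents predicts as few as 10 eligible people. The sample size was informed by recruitment rates from earlier observational work, and there are several identification routes. The example shows what the rule permits, not what is likely. The weekly pace is also conditional, since the dates follow the mention of professionals and may apply only to them. The 6-of-30 comparison does not depend on the dates.
- **Sites.** A reader might infer that one site could recruit everyone and the study would still pass. No condition sets a per-site minimum, but green also requires fidelity, and delivery is to be observed or recorded in all sites. Two empty sites would leave no delivery evidence there, so that reading is too strong.

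It is also fair to say that the figure of 30 was chosen for information, time and funding, not as a test of whether a full trial could recruit, and that a later trial could add sites or change routes. This argues for leaving the amber and red cut-offs to the committee. It does not argue for leaving recruitment out.

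**Conclusion.** The gap is real and of moderate weight. Applied exactly as written, the progression rule can give a Definite Go at any level of recruitment, provided that the shares are met and fidelity and acceptability are satisfactory. In the illustration this happens at 20% of the planned minimum. That the rule contains no recruitment number or rate rests on the text alone; the size of the shortfall rests on an assumed eligible count. This is not a detail left to a fuller document, because the criteria are set out here with numeric cut-offs. Reporting and committee discussion reduce the likely harm but do not close the gap. It should be fixed, but does not by itself invalidate the study.

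**What to change.** Add a recruitment-yield condition to the green and red lists in Criteria for progression to full trial. Green: the planned minimum of 30 dyads is reached within the recruitment period. The amber and red cut-offs should be fixed by the Trial Oversight Committee before it reviews the data; the documents give no basis for a particular figure. State that the committee considers green results as well as amber ones, and that it weighs recruitment per site and by identification route before a Definite Go is declared. State also whether the dates given in Recruitment, screening and consent are the recruitment window for dyads.

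The cost is a few lines of text and no new data collection, because the site lists and recruitment counts are already planned. The downside is that a Go becomes slightly harder to reach.
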